## Abstract

**Background:**

Breast neoplasms are the second most common type of cancer worldwide, and radiation therapy is a key component of their treatment. Acute skin reactions are one of the most common side effects of radiation therapy, and prevention of this adverse event has been investigated in several studies. However, a clinically applicable, preventative treatment remains unavailable. It has been demonstrated that application of a low-power laser can promote tissue repair. Therefore, the aim of this trial is to evaluate the effectiveness of an indium gallium aluminum phosphorus (InGaAIP) laser operated at 660 nm in preventing radiodermatitis in women undergoing adjuvant radiotherapy for breast cancer.

**Methods/Design:**

This is a two-arm, randomized controlled trial. A total of 52 patients undergoing radiotherapy for breast cancer (stages I to III) will be enrolled. Patients will be randomly assigned to an intervention group to receive laser therapy (n = 26) or a control group to receive a placebo (n = 26). The laser or placebo will be applied five days a week, immediately before each radiotherapy session. Skin reactions will then be graded weekly by a nurse, a radiotherapist, and an oncologist (all of whom will be blinded) using the Common Toxicity Criteria (CTC) developed by the National Cancer Institute and the Acute Radiation Morbidity Scoring Criteria developed by the Radiation Therapy Oncology Group. Patients will also answer a modified visual analogue scale for pain (a self-evaluation questionnaire). Primary and secondary outcomes will be the prevention of radiodermatitis and pain secondary to radiodermatitis, respectively.

**Discussion:**

The ideal tool for preventing radiodermatitis is an agent that mediates DNA repair or promotes cell proliferation. Application of a low-power laser has been shown to promote tissue repair by reducing inflammation and inducing collagen synthesis. Moreover, this treatment approach has not been associated with adverse events and is cost-effective. Thus, the results of this ongoing trial may establish whether use of a low-power laser represents an ideal treatment option for the prevention of radiodermatitis.

**Trial registration:**

ClinicalTrials.gov identifier: NCT02003599. Registered on 2 December 2013.

**Electronic supplementary material:**

The online version of this article (doi:10.1186/1745-6215-15-330) contains supplementary material, which is available to authorized users.

## Background

Approximately 90% of patients with breast cancer who are treated with adjuvant radiotherapy develop acute skin reactions [1]. Interventions to reduce this adverse side effect are needed since radiodermatitis may impact a patient’s adherence to treatment, and, with increased severity, can lead to the discontinuation of a potentially curative treatment [1, 2].

Acute radiodermatitis is a reaction caused by secondary skin exposure to ionizing radiation. Ionizing radiation impairs the ability of cells to proliferate quickly, and this leads to a skin reaction. This complex process involves DNA damage and changes in proteins, lipids, and carbohydrates. At the tissue level, this injury to the skin includes basal cell destruction and depletion of skin cells. As the migration of basal cells to the skin surface is compromised by radiation, flaking of the skin develops [1, 3]. Initially manifesting as erythema between the first and fourth weeks of radiation treatment, this condition can progress to ulceration up to three months after treatment [4, 5].

Known risk factors for radiodermatitis include total radiation dose, fractionation scheme, type of equipment used, volume of tissue irradiated (such as breast volume), and the radiosensitivity of the tissues involved. It is believed that patient-related factors, such as smoking habit, chronic diseases (including diabetes mellitus), and concomitant anticancer treatment can also interfere with skin reactions by affecting the healing process [6].

Prevention of this adverse event has been investigated in several studies [3, 7–9]. However, there is currently no clinically applicable prophylaxis available. As suggested by the Cancer Care Ontario Guidelines, the efficacy of topical agents remains controversial as well, and there is not sufficient evidence to indicate a prophylactic regimen using these agents for radiodermatitis.

Bolderston *et al*. [7] conducted a systematic review on the prevention and management of acute skin reactions related to radiation therapy. Unfortunately, the trials included in this systematic review were highly heterogeneous (the trials evaluated different kinds of treatments such as topical steroid creams, washing practices, sucralfate, Biafine cream, oral enzymes, amifostine, topical acid cream, aloe vera, chamomile cream, and dressings), and they concluded that there was insufficient evidence to support or refute specific topical or oral agents for the prevention or management of acute skin reactions [7].

Although various topical agents have been used to treat acute skin reactions, there is not sufficient evidence to establish a standardized recommendation for their application [3, 7]. In 2012, Zhang *et al*. [3] performed a meta-analysis on the use of topical agent therapy for the prevention and treatment of radiodermatitis. They concluded that topical agents could not prevent or treat radiodermatitis, probably because the topical agents chosen did not address the pathophysiology of radiodermatitis. An ideal agent for the prevention of radiodermatitis would mediate the repair of DNA damage or promote cell proliferation [3].

It was demonstrated that the cumulative effect of a low-power laser, when used at the appropriate dose, promoted tissue repair, possibly due to reduced inflammation and to the induction of collagen synthesis [10]. Specifically, laser treatment had a positive effect on injured fibroblasts by directly stimulating their growth, by affecting the expression of genes related to cell migration, DNA repair, ion channels, membrane potential, and cellular metabolism. It is hypothesized that the sum of these events contribute to ulcer healing through an increase in collagen synthesis, microcirculation, and suppression of apoptosis [11].

The application of a low-power laser for the prevention of oral mucositis is already well-established [12–15]. Moreover, the application of laser treatments to patients with breast cancer has also been found to be safe [16], and this method currently represents an option for treatment of lymphedema, a side effect of the surgical treatment of breast cancer [17–20]. Furthermore, a meta-analysis demonstrated that there are no side effects due to use of a laser during these treatments [14].

Previously, only one study has investigated the use of photomodulation by using light emitting diodes (LEDs) [21]. In this study, breast cancer patients were treated with radiation therapy following a lumpectomy, and LED photomodulation treatments were administered immediately following intensity-modulated radiation therapy (IMRT). These photomodulation treatments were found to reduce the incidence of skin reactions having a National Cancer Institute (NCI) grading of 1, 2, or 3 [21].

When laser therapy was applied to oral mucositis secondary to radiotherapy and chemotherapy, the incidence of grade 3 mucositis was reduced from 35.22 to 7.62% [22]. Based on these results, it is hypothesized that laser treatments may also represent a prophylaxis for radiodermatitis, particularly since there is currently no effective treatment for this side effect of radiotherapy. Therefore, this randomized controlled trial was designed to assess the effectiveness of laser therapy for the prevention of radiodermatitis.

## Methods/Design

### Study aims

The primary aim is to evaluate whether an indium gallium aluminum phosphorus (InGaAIP) laser operated at 660 nm can minimize the occurrence of radiodermatitis in breast cancer patients undergoing adjuvant radiotherapy. The secondary aim is to evaluate the ability of these laser treatments to decrease the pain associated with radiodermatitis.

#### Ethical issues

Ethical Committees of the Universidade do Vale do Sapucaí and the Hospital do Cancer de Barretos have approved this study protocol (approval numbers 564.777 and 626.876 respectively). Only participants who agree to provide written informed consent will be enrolled.

#### Study design and setting

This is a two-arm, parallel group, randomized controlled trial that will be conducted at the Hospital do Cancer de Barretos (Brazil), which treats annually approximately 600 patients who undergo adjuvant radiotherapy. Patients will be recruited from the radiotherapy department of this hospital.

#### Sample size

This study is powered to detect a reduction in the rate of radiodermatitis grade 3. To achieve an acceptable type 1 error of 5% and a type 2 error of 20%, the required sample size is 26 patients per arm (one-tailed test). We were not able to find data from breast cancer patients to use in the sample size calculation, thus it was performed based on data from the study of Bensadoun *et al*., which used a low-energy He/Ne laser to prevent radiation-induced mucositis in head and neck cancer patients [22]. These authors found not only a reduction in mucositis grade 3 (35.22% occurrence in control group versus 7.62% in laser group), but also a reduction in oral pain as assessed by patients, due to the preventive use of laser application.

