#### Group assignment

All patients undergoing radiotherapy for breast cancer will be assessed for eligibility criteria (including the dose of radiation) immediately after the radiotherapy planning. Eligible patients will be informed about the study and invited to participate. A total of 52 patients undergoing radiotherapy for breast cancer (stages I to III) will be prospectively enrolled after providing informed consent.

The participants will be allocated to an intervention group (laser therapy, n = 26) or a to a control group (placebo, n = 26). The latter will receive treatment from a deactivated laser unit that does not deliver radiation.

Group allocation will be determined using randomly generated computer sequences (Software R™, R Foundation for Statistical Computing, Vienna, Austria) [22]. The allocation concealment will be achieved by using a sealed opaque envelope with patient’s number in the study, which will be opened by the physiotherapist responsible for the intervention immediately before the first laser or placebo application.

The radiotherapist, the oncologist, the nurse, and the patients will be blinded to the allocation outcome. Only those administering the intervention (physiotherapist) will know the allocation of patients into the groups.

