#### Statistical analysis

Statistical analyses will be performed using Statistical Package for Social Sciences (SPSS) software v.18 (SPSS Inc., Chicago, Illinois, United States) and Software R™, (R Foundation for Statistical Computing, Vienna, Austria) [25]. The rejection level for the null hypothesis will be fixed at 5% (α ≤0.05). The pondered kappa coefficient will be used to compare responses among evaluators. The McNemar test will be used to compare levels of pain between groups (one test will be performed weekly). For inter-group assessments of the proportion of radiodermatitis, the Chi-square test will be used to compare group intervention and control.

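### The 26 per arm is sized for a one-tailed 5% test, but the analysis names a chi-square test at 5% with no tail; as ordinarily applied, its power is about 69–74%, not 80%

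*Protocol article*

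**What the plan says.** All references are to the protocol article, Methods/Design.

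- **Sample size.** The target is a single binary outcome: "This study is powered to detect a reduction in the rate of radiodermatitis grade 3". The error rates are "an acceptable type 1 error of 5% and a type 2 error of 20" (per cent), and the result is that "the required sample size is 26 patients per arm (one-tailed test"). The rates are borrowed from a trial of laser against mucositis in head and neck cancer: "35.22% occurrence in control group versus 7.62% in laser group".
- **Group assignment.** "A total of 52 patients undergoing radiotherapy for breast cancer (stages I to III) will be prospectively enrolled", split 26 and 26. The number enrolled therefore equals the number required.
- **Statistical analysis.** "The rejection level for the null hypothesis will be fixed at 5% (α ≤0.05"). For the proportion with radiodermatitis, "the Chi-square test will be used to compare group intervention and control". The section says nothing about one tail, two tails or a directional form of the test.
- **Baseline procedures and interventions, and Endpoints.** Patients are withdrawn for an adverse event attributed to the intervention or for withdrawn consent. They exit after a radiotherapy delay of more than 10 days not caused by radiodermatitis, or for missing weekly reviews. No expected rate is given.

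**The concern.** The Pearson chi-square statistic squares the difference between the arms, so at 5% (critical value 3.84) it rejects for a difference in either direction. A one-tailed 5% test of the same two proportions needs z of only 1.645 in the predicted direction, that is a squared value of 2.71. These are different decision rules, and the only power statement in the article belongs to the easier one.

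Two things are at stake. First, if the chi-square test is run as ordinarily applied, the type 2 error is 26–31% rather than the stated 20%, and a non-significant result would be read with more confidence than it deserves. Second, some results would be positive under one section and negative under the other. Take 7/26 events on placebo and 2/26 on laser. The pooled rate is 9/52 = 0.1731 and the difference is 5/26 = 0.1923. So chi-square = 0.1923² / (0.1731 × 0.8269 × 2/26) = 3.36, which lies between 2.71 and 3.84. The one-tailed test at 5% rejects and the ordinary chi-square test at 5% does not.

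**Working it through.** **Inputs.** Control rate p1 = 0.3522, laser rate p2 = 0.0762, alpha = 0.05, power 0.80 and one tail (Sample size); 26 per arm (Sample size, Group assignment); chi-square at 5% (Statistical analysis).

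Derived: difference d = 0.2760; mean rate = (0.3522 + 0.0762)/2 = 0.2142.

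- A = √(2 × 0.2142 × 0.7858) = √0.33664 = 0.5802
- B = √(0.3522 × 0.6478 + 0.0762 × 0.9238) = √0.29855 = 0.5464

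**Step 1: reproduce the plan's figure.** Pooled formula: n = (z_alpha × A + z_beta × B)² / d², with z_beta = 0.8416.

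- One-sided (z_alpha = 1.645): (0.9544 + 0.4599)² / 0.07618 = 26.25 per arm.
- The unpooled and arcsine one-sided formulas give 24.2 and 24.4.

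Strictly, 26.25 rounds up to 27, but 26 is within the spread of the usual formulas and gives the stated power to within half a point. So 26 reproduces as a one-tailed figure with no continuity correction and no allowance for losses.

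The two-sided version (z_alpha = 1.960) gives (1.1372 + 0.4599)² / 0.07618 = 33.48, so 34 per arm. Exact enumeration reaches 80.8% at 32 per arm.

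**Step 2: power at 26 per arm.** Normal approximation: power = Φ[(d√26 − z_alpha × A)/B], with d√26 = 1.4073.

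- One-sided: Φ[(1.4073 − 0.9544)/0.5464] = Φ(0.829) = 79.6%.
- Two-sided: Φ[(1.4073 − 1.1372)/0.5464] = Φ(0.494) = 68.9%.

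Exact power adds the probabilities of all pairs of binomial outcomes for which the uncorrected Pearson statistic rejects.

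| Test at 5%, 26 per arm | Pooled normal | Exact |
|---|---|---|
| One-tailed (Sample size) | 79.6% | 82.6% |
| Chi-square, two-sided (Statistical analysis as ordinarily read) | 68.9% | 73.6% |

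The unpooled and arcsine formulas give 73.1% and 72.7% for the two-sided test, within the same range. The shortfall against 80% is 80 − 73.6 = 6.4 to 80 − 68.9 = 11.1 points.

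**Step 3: losses.** Enrolment is 52 = 2 × 26, so the figures above need every patient to be evaluable. The documents give no loss rate, so the following is an assumption shown as a range. If patients were lost at random and dropped from the analysis, exact two-sided power would be:

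| Assumed loss | Exact two-sided power |
|---|---|
| 5% | 70.3% |
| 10% | 67.4% |
| 15% | 64.5% |
| 20% | 61.6% |

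**The case against.** The strongest reply is that the two sections can be read together. The Sample size section declares one tail and a direction, and the Statistical analysis section never says two-sided. For a 2×2 table, a one-tailed test can be run from the chi-square by halving its p-value when the difference lies in the predicted direction. On that reading the exact power is 82.6% and the stated 80% is met. Part of this stands: two-sidedness is inferred from the test named, and the power loss depends on that inference. But halving the p-value is a specific rule that amounts to a chi-square test at a nominal 10%, while the analysis section fixes the rejection level at 5% and gives no such rule. Nor is this detail that an article leaves to a fuller document, because the article itself fixes both the sizing and the test with its level, and the two do not match.

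Four stronger readings are tempting and not supported:

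- **The sample size is miscalculated.** It is not; Step 1 of the working reproduces it for the test it names.
- **Power is really below 60% because a corrected or exact test would be used.** The documents name neither. At the design rates the expected smaller cell is 26 × 0.2142 = 5.6 per arm, above the usual threshold of 5.
- **Exits certainly reduce the power further.** The article gives no rate and does not say that patients who exit leave the analysis. The loss figures are illustrations.
- **The tail will be chosen after the data are seen.** This is hypothetical. One tail and a direction were published while recruitment was still under way. What remains is that the analysis section leaves room for either rule.

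**Conclusion.** The concern holds as an inconsistency between the sizing and the planned test. The 80% power belongs to a one-tailed 5% test. The chi-square test at 5%, as ordinarily applied, has about 69% (pooled normal) to 74% (exact) with 26 per arm, a shortfall of about 6 to 11 points.

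This rests on three assumptions: the borrowed mucositis rates apply, the uncorrected Pearson test is used, and all 52 patients are evaluable. If 10–15% were lost from the analysis, exact two-sided power would be about 64–67%. If a directional test at one-sided 5% is what is meant, the stated power stands (before any losses) and the fault is only that the analysis section does not say so.

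**What to change.** Before unblinding, make the Sample size and Statistical analysis sections name the same test and the same tail, in one of two ways:

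1. **Two-sided.** State a two-sided Pearson chi-square test at 5% without continuity correction, and restate the power as about 69–74% with 26 evaluable per arm.
2. **One-sided.** If one tail is intended, write the directional test at one-sided 5% into the Statistical analysis section and keep the 80%.

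In either case, say that the power figure assumes no losses. If a loss rate is expected, state it as an assumption and give the power that follows.

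The cost is wording only, with no added patients. The downside of the first option is a less favourable stated power.

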#### Inclusion criteria

Female patients older than 18 years of age with a histological diagnosis of breast cancer (stages I to III) who underwent breast-conserving surgery or mastectomy without breast reconstruction with proposed adjuvant conventional radiotherapy according to the clinical protocol of Hospital do Cancer de Barretos (at full volume: ‘hot spot’ ≤115%, according to the International Commission on Radiation Units and Measurements (ICRU)) will be enrolled in this trial.

All patients will undergo radiotherapy according to the radiotherapy protocol of Hospital do Cancer de Barretos. The maximal point dose will not exceed 115% of the prescription whole breast dose (for example, the maximal point dose will not exceed 57.5 Gy for a prescribed dose of 50 Gy).

#### Exclusion criteria

Patients who have undergone a mastectomy with immediate breast reconstruction and those suffering from collagen diseases will be excluded from this study. Patients who do not meet the criteria for planning radiotherapy will also be excluded (patients with maximal point dose >115%).

#### Group assignment

All patients undergoing radiotherapy for breast cancer will be assessed for eligibility criteria (including the dose of radiation) immediately after the radiotherapy planning. Eligible patients will be informed about the study and invited to participate. A total of 52 patients undergoing radiotherapy for breast cancer (stages I to III) will be prospectively enrolled after providing informed consent.

The participants will be allocated to an intervention group (laser therapy, n = 26) or a to a control group (placebo, n = 26). The latter will receive treatment from a deactivated laser unit that does not deliver radiation.

Group allocation will be determined using randomly generated computer sequences (Software R™, R Foundation for Statistical Computing, Vienna, Austria) [22]. The allocation concealment will be achieved by using a sealed opaque envelope with patient’s number in the study, which will be opened by the physiotherapist responsible for the intervention immediately before the first laser or placebo application.

The radiotherapist, the oncologist, the nurse, and the patients will be blinded to the allocation outcome. Only those administering the intervention (physiotherapist) will know the allocation of patients into the groups.

#### Baseline procedures and interventions

Patients will undergo radiotherapy according to the radiotherapy protocol of Hospital do Cancer de Barretos. Protocols vary from 25 to 30 sessions of radiotherapy, taking into account the need of sequential tumor bed boost in some patients.

A pilot study was performed to adjust laser application methods, since there is no data about this in literature. For both intervention and control groups, a center point will be marked within an 18 × 18 cm [2] size area. Then, a plastic guide with a grid of 35 points will be centered over the surgical bed to guide the application of the laser or placebo (Figure 1). Five days a week, patients in intervention group will receive a laser treatment that is applied for 22 minutes (38 seconds each point) within 12 hours prior to each radiotherapy session. For the control group, the same procedure will be performed without activation of the laser. However, the appearance and noise of this placebo will be identical to the treatment group. In addition, both groups of patients will be blindfolded and will wear protective goggles during the treatments.

**Figure 1 Fig1:**
[figure not shown]
**Plastic guide with a grid of 35 points to guide the application of the laser or placebo.**

The center of the diagram is the meeting center of radiotherapy fields. In patients where this is not possible (patients radiating supraclavicular fossa), the nipple will be used as reference point for the center; and, in mastectomy patients, the midpoint between the tattoos will be used (as routine for radiation therapy, the patients undergoing radiation therapy in the hospital are routinely tattooed in two points, mid-axillary line and sternal; its midpoint roughly corresponds to nipple’s localization).

Patients allocated to the intervention group will receive laser treatments using a Photon Laser III (DMC™, São Carlos - SP, Brazil), approved by ANVISA (Agência Nacional de Vigilância Sanitária) for medicinal purposes. This InGaAIP laser emits a pulsed 660 nm beam with contact, with an average output of 80 mW. The laser energy is 3 J, with a power density of 80 mW and a dose emission of 108 J/cm [2]. The distribution of the light beam in the marking will be on points with a radius of 1 cm. Clinical and demographic data will be collected before the first radiotherapy session, including schemes of chemotherapy, breast volume, smoking habit, chronic diseases, and concomitant anticancer treatment, as they are factors that can interfere with the development of radiodermatitis.

After the second week of radiotherapy, patients will be evaluated for radiodermatitis weekly, after the laser or placebo application. They will also complete a modified visual analogue scale for pain (a patient self-evaluation questionnaire, validated for use in Brazil) [23]. Skin reactions and pain will be continue to be graded weekly until the end of treatment, and this evaluation will be independently performed by three previously trained evaluators: a nurse, a radiation oncologist, and an oncologist. The Common Toxicity Criteria (CTC 4.0), developed by the NCI [24], and the Acute Radiation Morbidity Scoring Criteria developed by the Radiation Therapy Oncology Group (RTOG) [5] will be used as guidelines.

The CTC was first described in 1982 and the version we will is the 4.0. It classifies radiodermatitis in degrees: 1 (faint erythema or dry desquamation), 2 (moderate to brisk erythema; patch moist desquamation, mostly confined to skin folds and creases; moderate edema), 3 (moist desquamation in areas other than skin folds and creases; bleeding induced by minor trauma or abrasion), 4 (life-threatening consequences; skin necrosis or ulceration of full thickness dermis; spontaneous bleeding from involved site; skin graft indicated) and 5 (death) [24].

Also in 1982, The RTOG developed the Criterion score for Acute Radiation Morbidity - Acute Radiation Morbidity Scoring Criteria, to classify the effects of radiotherapy. This criterion identifies grades 0 (no change over baseline), 1 (follicular faint or dull erythema, epilation, dry desquamation, decreased sweating), 2 (tender or bright erythema, patchy moist desquamations, moderate edema), 3 (confluent, moist desquamation other than skin folds, pitting edema) and 4 (ulceration, hemorrhage, necrosis) [5].

The visual analogue scale for pain was adapted and validated for use in Brazil by Ferraz *et al*. [23], in 1990. It is a patient self-evaluation scale, ranging from 0 to 10, with 0 meaning no pain and 10 meaning maximum pain [23].

Grading of radiodermatitis and pain assessment and will be repeated 90 days after the beginning of radiotherapy. If any of the evaluators perceive any adverse event that could be attributed to the intervention, or if the patient withdraws consent at any time, this patient will be immediately withdrawn from the study.

Both arms will follow the institutional skin care protocol, which consists of chamomile cream 10% with silicone cream 5.5%. This concoction will be used three times a day for the duration of the radiotherapy.

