#### Endpoints

Participation is in this study is considered complete 90 days after the beginning of radiotherapy. However, exit points include a delay in radiotherapy greater than 10 days (if the break is not caused by radiodermatitis), or non-attendance of the patient at weekly review sessions.

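### The plan names no pain score before laser or placebo treatment starts, although the secondary outcome is pain due to radiodermatitis; a lesser point is the single day-90 check after radiotherapy

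*Protocol article*

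**What the plan says.** On the start of assessment, Baseline procedures and interventions says: "After the second week of radiotherapy, patients will be evaluated for radiodermatitis weekly, after the laser or placebo application". The pain scale is completed on the same schedule, and "Skin reactions and pain will be continue to be graded weekly until the end of treatment".

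On data taken earlier, the same section says: "Clinical and demographic data will be collected before the first radiotherapy session, including schemes of chemotherapy, breast volume, smoking habit, chronic diseases"; concomitant anticancer treatment completes the list. The stated reason is that these factors can affect the development of radiodermatitis. No pain score appears, but the list opens with a word that leaves room for more.

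The Abstract gives the secondary outcome as prevention of pain due to radiodermatitis, and Study aims says the same in substance. The scale itself is a general 0-10 pain rating with no attribution to a cause. Inclusion criteria admits only women who have had breast-conserving surgery or a mastectomy. Statistical analysis compares pain between groups with a McNemar test each week.

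On the end of assessment: "Grading of radiodermatitis and pain assessment and will be repeated 90 days after the beginning of radiotherapy", and Endpoints adds "Participation is in this study is considered complete 90 days after the beginning of radiotherapy". The Background, after placing first erythema in weeks 1 to 4 of radiotherapy, says that "this condition can progress to ulceration up to three months after treatment".

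**The concern.** The secondary outcome concerns pain from a particular cause, but the instrument records pain from any cause. If the first score comes after two weeks of treatment, pain left by surgery cannot be told apart in the individual patient from pain caused by the skin reaction. Nor can the analysis remove the spread between patients that was there before treatment. A score taken at that point cannot serve as the baseline, because about 10 laser or placebo sessions may already have affected it. In a trial of 26 patients per arm, a chance difference in initial pain would go unseen.

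The follow-up point is separate. The last assessment is timed from the start of radiotherapy, whereas the period of possible progression in the Background is timed from its end. A reaction that appears and heals between the last weekly visit and day 90, or that appears after day 90, would not be graded.

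**Working it through.** **Sessions before the first pain score.** The Abstract and Baseline procedures and interventions give five applications a week. Two weeks × 5 = 10 sessions. If the wording is read as starting in week 2, about 5 sessions come first, and there is still no pre-treatment score.

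**Value of a baseline pain score.** The plan gives no figure to reproduce here. In a linear model for the 0-10 score with baseline as covariate, the residual variance is multiplied by 1 − r², where r is the correlation between baseline and later pain. The equivalent increase in patients is 1/(1 − r²) − 1. The documents give no r, so the values below are assumptions.

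| r | 1 − r² | Equivalent extra patients, all scored | Half scored |
|---|---|---|---|
| 0.3 | 0.91 | 10% | 5% |
| 0.5 | 0.75 | 33% | 17% |
| 0.6 | 0.64 | 56% | 28% |

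The last column reflects Trial status, which reports 26 of the planned 52 patients enrolled by the end of June 2014. If half the patients have no baseline score, relative information is about 0.5 + 0.5/(1 − r²). For r = 0.5 this is 0.5 + 0.667 = 1.167. If nearly all patients report no pain at the start, r is close to 0 and so is the gain.

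**Calendar of the follow-up.** The inputs are: "Protocols vary from 25 to 30 sessions of radiotherapy, taking into account the need of sequential tumor bed boost in some patients"; five sessions a week; no interruption; first session on a Monday, counted as day 1; three months taken as 91 days.

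- Last session: 25 sessions, 4 × 7 + 5 = day 33; 30 sessions, 5 × 7 + 5 = day 40.
- From the last session to day 90: 90 − 33 = 57 days; 90 − 40 = 50 days.
- Three months after the last session: 33 + 91 = day 124; 40 + 91 = day 131.
- Day 90 falls short of that limit by 124 − 90 = 34 days to 131 − 90 = 41 days.

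Counting whole weeks of radiotherapy (35 or 42 days) gives gaps of 55 and 48 days, so the result depends little on the convention. Endpoints makes a delay an exit point only beyond 10 days. A permitted 10-day delay would shorten the gap and lengthen the shortfall by 10 days each.

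**The case against.** The strongest objection is that the missing pain score is inferred from silence. The list of early data is a list of risk factors, it is expressly open-ended, and a journal article may leave visit details to the full protocol. This stands as a caveat. But the article does say when pain scoring begins, and a site following it as written would have no earlier score.

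Second, allocation is random, so pain already present does not bias the comparison. This stands. A reader might infer that the pain result would be invalid without a baseline; the documents do not support that. The loss is in precision, in protection against chance imbalance, and in attributing pain within a patient.

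Third, the planned McNemar test takes no covariate, so the gain above cannot be had under the stated analysis. This also stands, and the fix must therefore change the model as well as the form. That breast surgery leaves pain in some patients is likewise an assumption, not a statement in the protocol.

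On follow-up, the Background gives an outer limit, and ties it to ulceration. The RTOG scale places ulceration at grade 4, and CTC does so for full-thickness ulceration, whereas Sample size powers the trial on grade 3. The two operative statements about day 90 agree with each other, and both arms have the same schedule. A reader might infer that the primary comparison is biased or that many grade 3 events would be lost. Neither follows: an identical schedule does not by itself favour an arm, and the documents do not say how many reactions arise only in the gap.

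A reader might also infer that grading must start in week 1 and that a baseline skin grade is missing. The Background places first erythema, a milder stage, in weeks 1 to 4, and nothing suggests that grade 3 reactions come and go before week 3. Although RTOG grade 0 is defined relative to baseline, practically every patient would be grade 0 before any radiation, so that record would tell little.

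**Conclusion.** The point holds in a limited form. As the article is written, no pain score precedes treatment for an outcome defined as pain due to radiodermatitis in women who have all had breast surgery. The cost is precision and attribution, not validity. With an assumed correlation of 0.3 to 0.6 and a score from every patient, a baseline would be worth about 10% to 56% more patients for the pain comparison. If half the patients lack it, the figure is about 5% to 28%. If the full protocol already takes the score, only the choice of model remains.

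The follow-up point is secondary. About 50-57 days after radiotherapy have no planned assessment, and day 90 comes about 34-41 days before the limit in the Background, assuming uninterrupted treatment. This calls for reconciling the text or narrowing the conclusion. Grading in week 1, a baseline skin grade, an extra visit after radiotherapy and a later final visit are optional design choices; their absence is not an error.

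**What to change.** 1. Add the 0-10 pain score to the data already collected before treatment. State that it is taken before the first laser or placebo application, and preferably before the allocation envelope is opened. The present wording refers only to the first radiotherapy session, which the laser precedes.
2. Replace the weekly McNemar tests of pain with a between-group model that accepts the baseline score as covariate, for example a linear model for repeated weekly scores. State how patients without a baseline score are handled. Their scores are missing because of enrolment date, not treatment arm, so a missing-value indicator would serve.
3. Reconcile the three months after treatment in the Background with the day-90 statements in Baseline procedures and interventions and in Endpoints. Otherwise, say that conclusions apply to reactions seen at the weekly reviews during radiotherapy and at day 90.

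The cost is one self-rated item at an existing contact and a short amendment to the analysis. No visit is added. Up to half the patients may be past the point where the score can be taken, which reduces the gain but does not harm the comparison.
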